For the anlotinib hydrochloride capsules that have been distributed to the subjects, the remaining drugs of the last time should be recalled. For the drugs that have not been distributed to the subjects, they should be handed over to the co-organizers for disposal or destruction after the end of the trial together with the remaining drugs recovered during the trial.

- 1. **TQB2450preparation method**

Aseptic principles should be strictly followed during the preparation process. Under aseptic conditions, extract the desired dose of TQB2450from the glass bottle and aseptically dilute it with sterile, non-heated physiological saline to a total volume of 250ml in an infusion bag. Gently invert the solution without shaking to ensure adequate mixing.

As an injectable medication, it should be visually inspection for the presence of particulate matter and discoloration before administration. The drug is a clear to slightly opalescent, colorless to pale yellow liquid. If the solution appears cloudy, discolored, or in the presence of visible particles, it should be discarded. Do not shake the vial.

TQB2450 does not contain preservatives and IV bags containing TQB2450 must be used immediately after dilution/mixing. If the TQB2450 dilution cannot be used immediately, the method of storage is as follows:

- The total storage time from opening the TQB2450 vial to the end of injection should not exceed 6 hours at room temperature;
- The total storage time should not exceed 24 hours in the refrigerator of 2 ℃-8 ℃ without freezing and shaking.
  1. **Administration regimens of the study drugs**
     1. **Administration principles**

During the study period, every 21 days will be one treatment cycle. More than 3 days per treatment cycle will be considered as reasonably delayed dosing, the subsequent administration time was calculated according to the actual date of the previous administration. No other anticancer therapy was allowed during the medication. Patients with the disease control (CR+PR+SD) and who can tolerate adverse effects continue the medication until disease progression or intolerance.

- TQB2450: On the first day of each cycle (D1), a fixed dose of 1200mg will be administered intravenously using an infusion set with a filter membrane, and infused for 60 ±10 minutes. The infusion time starts with the beginning of the TQB2450 infusion and ends with the completion of the TQB2450 infusion and normal saline flushing.

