**Table 5.5-1 Adjustment measures for infusion reaction**

| Grades of AEs  (NCI-CTCAE v5.0) | Adjustment measures |
| --- | --- |
| Grade 1- mild  It is not recommended to interrupt the infusion and clinical intervention for transient mild reactions | The rate of drop was reduced by 50% and any worsening symptoms were closely observed, and clinical intervention was performed if necessary. |
| Grade 2- moderate  Treatment or fluids should be suspended and systemic therapy (e.g., antihistamines, nsaids, anesthetics, intravenous fluids) should be given immediately. Prophylactic therapy is recommended for 24 hours or less. | Treatment with TQB2450 was suspended and resumed when the infusion reaction had resolved to grade 0-1 with a 50% reduction in the infusion rate. During this period, any worsening symptoms were closely observed and appropriate therapeutic interventions were initiated according to local medical practices. |
| Grade 3- severe  Symptoms persist, such as a slow response to systemic therapy and suspension of infusions, relapses after rapid resolution, and hospital admission due to complications. | Treatment with TQB2450 was immediately and permanently discontinued, and appropriate therapeutic interventions were implemented according to local practice. |
| Grade 4- life-threatening and requiring urgent medical intervention |  |

If the infusion rate of TQB2450 is reduced by 50% (90±10min) because of an infusion reaction, this reduction must be maintained for the next scheduled infusion. If an infusion reaction was not observed at the next scheduled infusion, the infusion rate could be returned to the baseline rate during subsequent infusions.

- - 1. **Adjustment of administration regimens**
       1. **General principles for adjustment of administration regimens**

When a toxic reaction occurs, the investigator may refer to the following rules for delay or dose adjustment. The reason for the delay or dose adjustment, the supportive therapy taken and the results should be documented in the subject's medical record and EDC.

If the investigator determines that the dosing adjustment differs from the proposed adjustment rule, after consultation and communication with the sponsor, the investigator will make the appropriate adjustment with reference to clinical practice guidelines or previous clinical experience, and the relevant reasons will be recorded in the subject’s medical record.

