- Toxic reactions should be graded according to the NCI CTCAE 5.0;
- In case of simultaneous occurrence of severe toxicity of different severity levels, adjustments should be made according to the highest level observed;
- Treatment delays due to toxicity caused by anlotinib capsules could be delayed up to 35 days after the start of day 1 of the cycle (i.e., a 14-day delay in planned treatment) to allow adequate time for the subject to recover from any toxic effects caused by anlotinib hydrochloride. If a subject is unable to resume treatment by day 35 after the last dose, the subject must discontinue anlotinib hydrochloride treatment;
- Treatment delays due to toxic reactions caused by TQB2450 could be delayed up to 12 days after the start of day 1 of the treatment cycle;
- If subjects require permanent discontinuation due to toxic reactions (e.g., immune-related pneumonitis) of TQB2450, monotherapy with anlotinib should be continued until disease progression or unacceptable toxicity (whichever occurs first);
- If subjects require permanent discontinuation due to toxic reactions (hypertension, proteinuria, etc.) of anlotinib, monotherapy with TQB2450 should be continued until disease progression or unacceptable toxicity (whichever occurs first);
  - - 1. **Criteria for Dose Delay**

All of the following conditions should be met before starting treatment in any cycle, otherwise, a delay in administration is required:

- Absolute neutrophil count ≥1.5×109/L;
- Platelet count ≥75×10^9^/L;
- Hemoglobin（Hb）≥80g/L;
- Proteinuria ≤2+;
- Hand-foot skin reaction and hypertension ≤grade 2;
- Other toxicities until recovery to ≤grade 1

During the administration period (1-14 days) of anlotinib every cycle, if toxic reactions occur and the medication needs to be delayed, the maximum delay time should not exceed 5 days. If the medication cannot be continued for more than 5 days, the remaining anlotinib will not be administrated in this cycle.

- - - 1. **Dose modification**

Dose modifications for the TQB2450 were not allowed in principle throughout the study.

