**Table 5.5-10 Treatment of immunogenic adverse reactions**

| Immunologically adverse reactions related to the trial drugs | Severity (CTC grade of AEs) | Clinical Management |
| --- | --- | --- |
| Respiratory diseases  (e.g., interstitial pneumonia) | Grade 2 | Suspend treatment and provide symptomatic treatment with glucocorticoids until toxicity subsides to Grade 1 or lower. If toxicity does not recover within 12 weeks after the last administration, treatment should be terminated. |
|  | Grade 3 or worse, or recurrence | Discontinuation of treatment |
| Hepatitis | Grade 2 (3×ULN < ALT or AST < 5×ULN, or 1.5×ULN < total bilirubin < 3×ULN), lasts for more than 5 days | Suspend treatment and provide symptomatic treatment with glucocorticoids until toxicity subsides to Grade 1 or lower. If toxicity does not recover within 12 weeks after the last administration, treatment should be terminated. |
|  | Grade 3 or worse (ALT or AST≥5×ULN, or total bilirubin ≥ 3×ULN） | Discontinuation of treatment |
| Colitis or diarrhea | Grade 2 or 3 | Suspend treatment and provide symptomatic treatment with glucocorticoids until toxicity subsides to Grade 1 or lower. If toxicity does not recover within 12 weeks after the last administration, treatment should be terminated. |
|  | Grade 4 | Discontinuation of treatment |
| Pancreatitis | Grade 2 or 3 pancreatitis  Grade 2 or 3 elevated amylase or lipase | Suspend treatment and provide symptomatic treatment with glucocorticoids until toxicity subsides to Grade 1 or lower. If toxicity does not recover within 12 weeks after the last administration, treatment should be terminated. |
|  | Grade 4 or recurrent pancreatitis | Discontinuation of treatment |
| Endocrine dysfunction | Grade 2 or 3 hypophysitis | Suspend treatment and provide symptomatic treatment with glucocorticoids until toxicity subsides to Grade 1 or lower. If toxicity does not recover within 12 weeks after the last administration, treatment should be terminated. |
|  | Grade 4 hypophysitis | Discontinuation of treatment |
|  | Hyperglycemia of grade 3 or higher (fasting blood-glucose >13.9-27.8 mmol/L） | Suspend treatment and use insulin replacement therapy until blood glucose levels recover to Grade 2 or below and remain stable. |

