|  | Symptomatic hypothyroidism Symptomatic hyperthyroidism, or asymptomatic hyperthyroidism with TSH＜0.1mIU/L | Suspend treatment and use relevant symptomatic treatment until the relevant indicators recover to the inclusion criteria. |
|  | Adrenal insufficiency of grade 2 or higher | Suspend treatment and provide symptomatic treatment with glucocorticoids until toxicity subsides to Grade 1 or lower. If toxicity does not recover within 12 weeks after the last administration, treatment should be terminated. |
| Encephalitis or meningitis | All grades | Discontinuation of treatment |
| Motor and nervous system diseases | Grade 2 | Suspend treatment and provide symptomatic treatment with glucocorticoids until toxicity subsides to Grade 1 or lower. If toxicity does not recover within 12 weeks after the last administration, treatment should be terminated. |
|  | Grade 3 or worse, or recurrence | Discontinuation of treatment |
|  | All grades of Guillain-Barre syndrome | Discontinuation of treatment |
|  | All grades of myasthenia gravis | Discontinuation of treatment |
| Diseases of the skin and subcutaneous tissue | Grade 2 or 3 | Suspend treatment and provide symptomatic treatment with glucocorticoids until toxicity subsides to Grade 1 or lower. If toxicity does not recover within 12 weeks after the last administration, treatment should be terminated. |
|  | Grade 4 | Discontinuation of treatment |
| Eye diseases | Grade 2 | Suspend treatment and provide symptomatic treatment with glucocorticoids until toxicity subsides to Grade 1 or lower. If toxicity does not recover within 12 weeks after the last administration, treatment should be terminated. |
|  | Grade 3 or worse, or recurrence | Discontinuation of treatment |
| Other immune-related adverse events | Grade 2 or 3 | Suspend treatment and provide symptomatic treatment with glucocorticoids until toxicity subsides to Grade 1 or lower. If toxicity does not recover within 12 weeks after the last administration, treatment should be terminated. |
|  | Grade 4 | Discontinuation of treatment |

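### The TQB2450 toxicity-delay limit in section 5.5 (12 days after cycle day 1) is wrong as written and contradicts the 12-week recovery limit in ten rows of Table 5.5-10

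*Protocol*

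**What the plan says.** Protocol section 5.5, Administration principles, sets the schedule: "During the study period, every 21 days will be one treatment cycle", and for TQB2450 "On the first day of each cycle (D1), a fixed dose of 1200mg will be administered intravenously".

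The general principles for adjusting administration give each drug its own limit on toxicity delays. For anlotinib, treatment "could be delayed up to 35 days after the start of day 1 of the cycle (i.e., a 14-day delay in planned treatment"; a patient who cannot resume by then must stop anlotinib. For TQB2450, delays for "toxic reactions caused by TQB2450 could be delayed up to 12 days after the start of day 1 of the treatment cycle". No equivalent in days of delay is given for TQB2450, and no consequence for passing the limit.

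The Criteria for Dose Delay that follow begin "All of the following conditions should be met before starting treatment in any cycle, otherwise, a delay in administration is required". The last condition is that toxicities not otherwise listed have come down to grade 1 or lower.

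Table 5.5-10 covers immune reactions. Ten of its rows suspend treatment, prescribe glucocorticoids and close with "If toxicity does not recover within 12 weeks after the last administration, treatment should be terminated". One of the ten is a catch-all: "Other immune-related adverse events | Grade 2 or 3 | Suspend treatment and provide symptomatic treatment with glucocorticoids".

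The infusion-reaction text in section 5.5 requires systemic steroids given for infusion or immune-related reactions to be tapered over at least 2 weeks before the next dose.

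**The concern.** The bullet fails in two ways. Taken literally, it sets a limit that expires before the dose it is meant to govern has fallen due, while the Criteria for Dose Delay in the same section oblige the site to delay. Taken generously, it still sets a much shorter limit than the table that handles the same immune toxicities.

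Take a patient whose immune toxicity settles after the bullet's limit but within 12 weeks. That patient remains eligible for the antibody under Table 5.5-10 and is already out of time under the bullet. Section 5.5 moves patients who permanently stop TQB2450 to anlotinib alone. In a multicenter single-arm study of the combination, sites that follow different limits could therefore treat the same event differently.

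**Working it through.** Only calendar arithmetic is needed. All days are counted from day 1 of the current cycle, which is the day of the last TQB2450 dose.

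**Inputs**
- Cycle length: 21 days, with TQB2450 on day 1 (section 5.5, Administration principles).
- Anlotinib limit: 35 days after day 1, stated to equal a 14-day delay (section 5.5, general principles).
- TQB2450 limit: 12 days after day 1 (same list).
- Table limit: recovery within 12 weeks of the last administration (Table 5.5-10). The table does not name the drug; I take it to mean the last TQB2450 dose.
- Steroid taper: at least 2 weeks, or 14 days, before the next dose (section 5.5, infusion reactions).

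**Step 1. Reproduce the protocol's own figure.** Delay = limit − cycle length. For anlotinib, 35 − 21 = 14 days, as stated. The clock in this list therefore runs from day 1 of the current cycle.

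**Step 2. Put TQB2450 on the same clock.** 12 − 21 = −9 days. The limit passes 9 days before the next dose is due, so no delay is possible.

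**Step 3. Alternative reading.** If the clock starts at the scheduled day 1 of the delayed cycle, the limit is 21 + 12 = 33 days after the last dose. That is a workable 12-day delay.

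**Step 4. Compare with the table.** 12 weeks × 7 = 84 days for recovery. TQB2450 cannot restart under these rows before recovery. A recovery after day 12 (or after day 33 on the alternative reading) and up to day 84 is therefore acceptable to the table but already past the bullet's limit.

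**Step 5. Count the affected rows.**
1. Respiratory, grade 2
2. Hepatitis, grade 2
3. Colitis or diarrhea, grade 2 or 3
4. Pancreatitis or raised enzymes, grade 2 or 3
5. Hypophysitis, grade 2 or 3
6. Adrenal insufficiency, grade 2 or higher
7. Motor and nervous system, grade 2
8. Skin, grade 2 or 3
9. Eye, grade 2
10. Other immune-related events, grade 2 or 3

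The hyperglycemia and thyroid rows suspend treatment without a time limit and are not part of the conflict.

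**Step 6. Check the taper.** 14 days is longer than 12, so the taper alone overruns the literal limit. On the day-33 reading it must begin by day 33 − 14 = 19. If it begins on the due date, the earliest restart is 21 + 14 = 35, which is past day 33.

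**The case against.** The strongest defence is that these rules guide rather than bind. Section 5.5 says "the investigator may refer to the following rules for delay or dose adjustment" and allows departures after consulting the sponsor. The text before Table 5.5-10 only recommends the table. The TQB2450 bullet, unlike the anlotinib one, attaches no consequence to passing the limit. A site could also reasonably let the specific table prevail over a general bullet. All of this stands and lowers the practical weight. It does not settle the matter, because freedom to depart from a rule does not tell a site which of two limits applies, and no visible text ranks them.

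It is also fair to say that the 9-day figure depends on the reading of the clock. The anlotinib bullet supports that reading, but the day-33 reading is possible. The contradiction with the table survives both.

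A reader might infer more than the documents support:
- **That day 84 is the latest permitted restart, so that the gaps of 84 − 12 = 72 or 84 − 33 = 51 days measure lost restart time.** The table sets a deadline for recovery. A patient who recovers near day 84 and still has to complete the taper may restart later.
- **That days were written for weeks.** A slip of unit would explain the bullet, since 12 weeks would match all ten rows. The protocol does not confirm it.
- **That the suspend rows concern only the antibody.** The table's heading refers to the trial drugs in the plural, so narrowing the hold to TQB2450 would be a new safety decision.
- **That sample size, power or the PFS analysis is affected.** Nothing in this point touches them.

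**Conclusion.** The bullet is wrong as written. It permits no delay on the clock of its neighbouring rule, or stops at day 33 on the generous reading. In both cases it conflicts with ten rows of Table 5.5-10 that allow up to 84 days for recovery. The steroid taper adds a second mismatch with the literal 12 days.

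The conclusion rests on two assumptions: the table's last administration is the last TQB2450 dose, and its 12 weeks limits recovery, as its wording says. The documents give no event rate for this combination, so the number of patients affected is not estimated. The advisory status of the rules makes this a dosing inconsistency worth correcting, with no threat to the trial's statistical conclusions.

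**What to change.** First have the sponsor confirm the intended unit.

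If 12 weeks was meant, replace the TQB2450 bullet in section 5.5 with:

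> TQB2450 may be delayed for toxicity until the recovery required by Table 5.5-10 and the infection and liver rules that follow it. Where the table sets a 12-week limit, TQB2450 is permanently discontinued if toxicity has not recovered within 12 weeks after the last TQB2450 administration. The steroid taper in section 5.5 must be completed before restart.

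This ties the 12 weeks to recovery, so that a taper completed after week 12 does not create a new conflict. It also leaves the shorter infection and liver rules in force.

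If a 12-day delay past the due date was meant, write 33 days after day 1 (a 12-day delay) and change the ten table rows to match. In that case the taper would have to start by day 19.

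Two changes should not be made. Leave the instruction to suspend treatment in the table as it is, without limiting it to TQB2450. Do not add a 12-week stopping rule to the hyperglycemia or thyroid rows.

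The cost is a small amendment: one bullet, or one bullet and ten rows on the second option. Section 9.4 requires approval by the ethics committee and the sponsor before use, and sites must be notified. No patients or visits are added.

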| Dropout/Removal Criteria | - 1. Participants who do not meet the screening criteria;   2. Participants who are unable to evaluate for efficacy or unable to evaluate safety without receiving 1 dose of the drug;   3. Participants who are treated with chemotherapy, surgical or experimental drugs other than this protocol during the trial;   4. Participant's concurrent use of China Food and Drug Administration (CFDA)-approved modern herbal agents and immunomodulatory agents for the treatment of tumors;   5. Participants who do not follow the dose, method, and course of treatment according to the study protocol. |
| Termination Criteria | Subject must termination the study if the following cases occur (including but certainly not limited to):   - 1. Disease progression (PD) determined according to RECIST 1.1 criteria or considered clinically progressive.   2. Termination of treatment decided by the investigator from the patient's best interests.   3. Occurrence of intolerable adverse reactions or severe adverse events confirmed by the investigator.   4. Patients with poor compliance, using drug amounts outside the range of 80% to 120% of the prescribed dose.   5. Patient withdrawal of informed consent.   6. Initiation of other anti-tumor drug treatments affecting efficacy judgment (such as chemotherapy, targeted therapy, or biologic agents).   7. Unexpected pregnancy. |
| Study Schedule | Estimated date of the start of the study: August 2019  Estimated enrollment date of the last subject: August 2020  Estimated date of the end of the study: August 2021 |
| Study Procedures | TQB2450 plus anlotinib hydrochloride capsules were administered in a 21-day cycle until disease progression or intolerance. |
| Primary effect endpoints | Duration of response (DoR); overall survival (OS); 12-month progression-free survival rate; disease control rate (DCR); objective response rate (ORR) (assessed per RECIST version 1.1 at the following time points: 3 weeks after the first therapy, then every 6 weeks thereafter during therapy.) |
| Primary safety endpoints | Dose-limiting toxicities (DLT); maximum tolerable dose (MTD); vital signs; laboratory index; adverse event (AE); immune-related adverse event (irAE); serious adverse event (SAE) according to NCI CTCAE version 5.0. |

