     1. Decisions to withdraw from the study by the investigator

The investigator has the right to decide whether to withdraw from the study if a subject who has been enrolled in the study has any situation that is not suitable for continuing the study:

1. Participants who do not meet the screening criteria;
2. Participants who are unable to evaluate for efficacy or unable to evaluate safety without receiving 1 dose of the drug;
3. Participants who are treated with chemotherapy, surgical or experimental drugs other than this protocol during the trial including CFDA-approved modern herbal agents and immunomodulatory agents for the treatment of tumors
4. Participants who do not follow the dose, method, and course of treatment according to the study protocol with poor compliance using drug amounts outside the range of 80% to 120% of the prescribed dose.
5. Occurrence of intolerable adverse reactions or severe adverse events confirmed by the investigator.
6. Termination of treatment decided by the investigator from the patient's best interests.
   - 1. Decisions to withdraw from study by the subject

According to the CIF, the subjects participate in the trials voluntarily and have the right to withdraw at any stage of the trial without discrimination or retaliation and without affecting their medical treatment, rights, and interests; participants who were no longer receiving medications, leading to lost to follow-up without explicit withdrawal from the study, are considered as “withdrawal” or “dropout”. There are possible reasons for withdrawal from study:

- 1. Patient withdrawal of informed consent.
  2. The patient lost to follow-up for various reasons
     1. Subsequent data collection

The investigator must clearly document the reasons and timing for a participant's withdrawal, perform relevant observations and evaluations, complete the assessment according to the study's withdrawal criteria, and record these details in the relevant source documents, detailing the cause of withdrawal.

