For anlotinib hydrochloride capsules, according to the 3+3 dose climbing test, the maximum tolerated dose was determined as the initial dose. If the initial dose is 12mg, dose level 1 is 10mg, and dose level 2 is 8mg; If the initial dose is 10mg, dose level 1 is 8mg; If the initial dose is 8mg, there was no down-dose selection. Any subject who required a reduction in the anlotinib capsule dose would continue to receive the reduced dose for subsequent cycles. Any subject who has undergone two dose reductions and requires a third reduction due to toxic reactions must discontinue the study treatment.

Principles of dose modifications related to anlotinib hydrochloride capsules.

- Hematologic toxicity

1. Thrombocytopenia

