**(2)** **Hypertension**

In previous studies, anlotinib is associated with the frequent occurrence of hypertension and the incidence of grade 3 or higher hypertension was 13.61%. During this study, subjects are recommended to monitor blood pressure during treatment. In the event of a hypertensive event, the following managements are recommended:

Grade 1: Pre-hypertension (systolic blood pressure [SBP] 120-139 mmHg or diastolic blood pressure [DBP] 80-89 mmHg); No indication for antihypertensive drugs and blood pressure is monitored.

Grade 2: Stage 1 hypertension (SBP 140-159 mmHg or DBP 90-99g mmHg); Medical intervention is required. For recurrent or persistent (≥24 hours), symptomatic hypertension with >20mmHg SBP increases or >140/90 mmHg increase of previously normal range, monotherapy and blood pressure monitoring are required. Thiazide diuretic, angiotensin-converting enzyme inhibitors (ACEI), angiotensin II receptor blockers (ARB), beta-blocker, or calcium-channel blocker are commonly used.

Grade 3: Stage 2 hypertension (SBP ≥160 mmHg or DBP ≥100 mmHg); Medical intervention is required. Multidrug therapy is required, commonly using a thiazide diuretic combined with an ACEI, beta-blocker, or calcium-channel blocker.

Grade 4: Life-threatening (e.g., malignant hypertension, persistent neurological deficit, hypertensive crisis). Urgent treatments are required.

Hypertension emergencies: SBP >120 mmHg accompanied by acute or progressive target organ damage (e.g., Cerebral infarction, intracranial or subarachnoid hemorrhage, hypertensive encephalopathy, etc.); among them, the progressive or rapidly progressive hypertension based on chronic essential hypertension is the most common (about 40%-50%).

Hypertension urgencies: SBP >120 mmHg with no or minor organ damage.

In case of hypertensive crisis, subjects should discontinue the study treatment and withdraw from the study.

When subjects occur elevated blood pressure during vital sign measurements, a second measurement should be taken after a 15-minute rest. If the elevation is repeated and reaches the grade 2, it can be defined as an AE of hypertension. If the time of improvement from the first occurrence of hypertension to its reappearance is less than 1 week, it is identified as one AE and record the highest level of severity. The start time is defined as the time of the first hypertensive episode, and the end time is defined as the last outcome time of hypertension.

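### For some patients who must permanently stop anlotinib for toxicity, the protocol both continues TQB2450 alone and ends study treatment or participation; the section 8.2 one-year progression-free rate depends on which rule is followed

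*Protocol*

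**What the plan says.** **The single-drug rule.** Under the general principles for adjustment of administration regimens (section 5.5): "If subjects require permanent discontinuation due to toxic reactions (hypertension, proteinuria, etc.) of anlotinib, monotherapy with TQB2450 should be continued until disease progression". The sentence goes on to add unacceptable toxicity as a second end point for the monotherapy, whichever comes first. The bullet before it gives the mirror rule when TQB2450 is the cause. The same list sets a 35-day limit on anlotinib delays; a patient who exceeds it is told that "the subject must discontinue anlotinib hydrochloride treatment", which stops one drug only.

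**Rules that go further.**
- Dose modification (section 5.5): a subject who "has undergone two dose reductions and requires a third reduction due to toxic reactions must discontinue the study treatment".
- Hypertension, under common adverse events related to anlotinib (section 6.5.6.2): "In case of hypertensive crisis, subjects should discontinue the study treatment and withdraw from the study".
- Synopsis, Termination Criteria: "Subject must termination the study if the following cases occur", and one listed case is "Occurrence of intolerable adverse reactions or severe adverse events confirmed by the investigator". The list does not separate toxicities by causal drug. Section 4.5 lists the same event, but there "The investigator has the right to decide whether to withdraw from the study".

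**Rules that do not say which drug.** The anlotinib tables for platelets (5.5-2), bleeding (5.5-6), hypertension (5.5-7) and other non-hematologic toxicity (5.5-9) prescribe permanent termination of treatment at their top grades without naming the treatment.

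**Endpoint rules.** PFS (sections 6.4 and 8.2) is censored at discontinuation when a patient stops for a reason other than progression and has no later tumor imaging, or at the start of subsequent therapy. Section 6.4 defines the one-year PFS rate by progression or death. Section 8.2 adds withdrawal due to intolerance as an event for the one-year progression-free rate.

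**The concern.** A site following the general principles keeps a patient who can no longer take anlotinib on TQB2450. A site following one of the other rules stops both drugs and may end participation. In a multicenter single-arm trial that means different treatment for patients with the same toxicity, with no stated order of precedence to settle it.

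The choice also affects how outcomes are counted. A patient who stays on TQB2450 remains in the study. The same patient withdrawn for hypertensive crisis fits section 8.2's category of withdrawal due to intolerance, and so becomes an event in the one-year progression-free rate without having progressed or died.

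**Working it through.** The protocol states no figure on this point to reproduce, so the main check is to set the rules side by side for each route to a permanent anlotinib stop.

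| Route | General principles, 5.5 | Other rule | Conflict? |
| --- | --- | --- | --- |
| Delay beyond 35 days | Stop anlotinib only | – | None |
| Hypertensive crisis | Continue TQB2450 (hypertension is a named example) | 6.5.6.2: stop study treatment and leave the study | Yes, direct |
| Third anlotinib reduction needed for toxicity | Continue TQB2450 | Dose modification: stop study treatment | Yes, as worded |
| Intolerable reaction to anlotinib | Continue TQB2450 | Synopsis: must terminate. Section 4.5: investigator decides | Less firm |
| Top grade in Tables 5.5-2, 5.5-6, 5.5-7, 5.5-9 | Continue TQB2450 | Treatment ends, drug not named | Ambiguous |

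Three points support the two firm rows.

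1. Section 6.5.6.2 gives hypertensive crisis as an example of grade 4 hypertension, and Table 5.5-7 ends treatment permanently at grade 4. The crisis patient is therefore one whose anlotinib is permanently stopped for hypertension, which is the general principles' own example.
2. When section 5.5 means one drug, it names it, as the 35-day rule shows. The third-reduction rule uses the broader term.
3. The third-reduction route can occur. The synopsis gives 12 mg as the phase II dose, and the dose-modification section provides two steps down from it.

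**Effect on time-to-event PFS.** The notes to the Study Procedures table follow patients who withdraw without objective progression until progression or data cut-off. They also require a scan at end of treatment, then further tumor assessment (every 8 weeks in the notes, every 6 weeks in the table) until progression or new therapy. The note on time to progression applies this expressly to intolerance. The waiver of later data collection in section 4.5 does not list toxicity as a reason. So under either treatment rule the patient should still be scanned, and a later progression counts. Censoring arises only if scans are missed or new therapy starts.

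**Effect on the one-year rate.** Inputs: 54 patients (section 3.3) and the design median PFS of 9 months.

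- One patient: 1/54 = 1.9 percentage points. This is the most that one reclassified patient can move the rate if no other patient is censored before one year.
- Illustration. Assume exponential PFS with median 9 months, and withdrawals for intolerance that occur independently of progression, with probability *q* by one year. The protocol gives no *q*; 5% to 20% is an assumption.
  - Progression or death only: exp(−12 × ln 2 / 9) = 39.7%.
  - Withdrawal for intolerance also an event: 39.7% × (1 − *q*) = 37.7% at *q* = 5% and 31.7% at *q* = 20%.

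The gap of 2.0 to 7.9 points is for all withdrawals for intolerance. The disputed routes are only part of these, so their share is smaller.

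**The case against.** The strongest reply is that these are specific rules beside a general one. Hypertensive crisis and a third reduction are particular situations; in the anlotinib paragraph, study treatment could be read as anlotinib; the synopsis list is generic; the monotherapy rule has its own exit for unacceptable toxicity; and section 5.5 lets the investigator depart from its rules after consulting the sponsor.

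Part of this stands. The two firm conflicts cover particular routes, not every anlotinib stop. The synopsis item is weak evidence because section 4.5 makes it discretionary, and the tables are ambiguous rather than contradictory. The rest does not remove the conflict. No precedence is stated, and the general principles name both the drug and the toxicity. The unacceptable-toxicity exit cannot refer to the anlotinib reaction that triggered the switch, or the monotherapy rule would never apply. Latitude to depart from a default does not reconcile two opposite defaults, and the third-reduction rule is worded as an obligation.

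A reader might also infer that toxicity-limited patients are PFS events under one rule and censored under the other, costing the primary analysis events and power. The documents do not support that. Imaging continues after a stop without progression, and censoring at discontinuation applies only where no later imaging exists. The protocol gives no rate from which to derive lost events, and the planned 32 events already sit beside a 20% loss allowance. No power figure is therefore offered.

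**Conclusion.** The protocol contradicts itself for at least two groups: patients with hypertensive crisis and patients who need a third anlotinib reduction. The synopsis criterion adds a weaker conflict, and four anlotinib tables leave open which treatment ends. The first consequence is that treatment of these patients depends on the page followed.

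For the primary PFS analysis the consequence is conditional on missed scans or new therapy. For the section 8.2 one-year progression-free rate it is direct: each patient reclassified as withdrawn for intolerance moves it by up to about 1.9 points. This is clearest for hypertensive crisis, where the text says the patient leaves the study. The third-reduction rule ends treatment but does not say whether that counts as withdrawal. The 2.0 to 7.9 point range rests on an assumed 5% to 20% one-year withdrawal rate, exponential PFS with median 9 months, and independence; it is an illustration, not an estimate. The disagreement between the two one-year definitions remains however the treatment rules are settled.

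**What to change.** 1. Reconcile the synopsis Termination Criteria, section 4.5, the general principles and dose-modification text in section 5.5, Tables 5.5-2, 5.5-6, 5.5-7 and 5.5-9, and the hypertension text in section 6.5.6.2. Each should say whether anlotinib, both drugs or study participation ends. Which applies to which toxicity is the sponsor's clinical decision, and this review takes no position on it.
2. At each of those places, cross-refer to the existing rule in the Study Procedures notes that tumor and survival follow-up continues after a stop for toxicity.
3. Use one definition of the one-year progression-free rate in sections 6.4 and 8.2, stating whether withdrawal due to intolerance is an event.

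The cost is a wording amendment, with ethics committee approval as section 9.4 requires. It adds no patients, visits or procedures.
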